### Help-seeking and use of treatment

The instrument selected consists of two parts: (i) the first question asks whether the person has received psychological and/or medicinal treatment for an MH problem at any time in her/his life; and (ii) the second part includes the first item from the Spanish version of the ***General Help-Seeking Questionnaire (GHSQ)*** for measuring help-seeking behaviour in adolescents [46, 47]. The GHSQ asks participants to respond to each problem-type by rating their help-seeking intentions on a 7-point scale ranging from 1 (“extremely unlikely”) to 7 (“extremely likely”) for each help source option including “no one.” The sum of the points gives a total score ranging from 5 to 35. Higher scores indicate higher help-seeking intentions. Additionally, we added an econometric questionnaire of 8 items on the use of services for the purpose of the cost-effectiveness study.

**Health Benefits Questionnaire:** 17-item questionnaire to include information about: a) family: parental age, studies and occupation; number of brothers/sisters and their ages; b) academic scope: years in the same school, repeated school years, average grade, number of failed subjects and number of written warnings; and c) health: difficulty sleeping and general state of health.

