A secondary hypothesis to be tested will be: participation in the intervention groups (SP, MHL and MHL + SR) will reduce mental health symptoms, increase emotional well-being and help-seeking behaviours, reduce bullying and cyberbullying at school, and improve HRQoL immediately after 2 weeks, 6 months and 12 months post-intervention, compared to a waiting list control group.

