### Measures

The variables and instruments selected, as well as the evaluation programme timeline, are detailed in Table 3. Collected data will then be imported using a teleform format program onto a computer database.

**Table 3 Tab3:** Outcome measures

Outcome measures	Timeline			
	Pre-intervention	Post-intervention		
		2 w	6 mo	12 mo
Primary outcomes				
1. Mental Health Knowledge				
EspaiJove.net Mental Health Literacy Questionnaire (EMHLQ)	X	X	X	X
2. Behaviour and Attitudes Towards Mental Health (Stigma)				
Reported and Intended Behaviour Scale (RIBS)	X	X	X	X
The Scaling Community Attitudes toward the Mentally III (CAMI) - Authoritarianism subscale	X	X	X	X
Others outcomes				
3. Acceptability and satisfaction				
Satisfaction questionnaire		X		
4. Mental Health Symptoms and Emotional Well-Being				
Strengths and Difficulties Questionnaire (SDQ)	X	X	X	X
5. Bullying and Cyber-Bullying Behaviours				
Bullying and Cyber-Bullying Questionnaire	X	X	X	X
6. Intentions to Change				
Intentions to Change Questionnaire (ICQ)	X	X	X	X
7. Health-related quality of life				
EuroQol Questionnaire (EQ-5D-5 L)	X	X	X	X
8. Help-seeking				
General Help-Seeking Questionnaire (GHSQ)	X		X	X
9. Use of Health Services and Treatment				
Use of Health Services and Treatment questionnaire	X		X	X
10. Health Benefits Questionnaire				
Familiar, academic and general health questions	X		X	X

*Abbreviations*: *mo* months, *w* weeks

First of all, socio-demographic variables will be collected: age; date of birth; gender; nationality; city/village; neighbourhood of residence or postcode. The following variables are listed below:

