### Bullying and cyber-bullying behaviours

Four yes/no questions were specially developed for the purposes of this study to ask whether a person has been a victim or a perpetrator of a bullying and/or a cyberbullying incident.

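### The treatment-use question has a lifetime window but is repeated at 6 and 12 months, so an unadjusted follow-up comparison of this outcome is diluted towards no difference (minor).

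*Protocol article*

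**What the plan says.** All references are to the protocol article.

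- **The question.** The section Help-seeking and use of treatment describes a two-part instrument. The first part asks "whether the person has received psychological and/or medicinal treatment for an MH problem at any time in her/his life". The second part takes one item of the GHSQ, with pupils "rating their help-seeking intentions on a 7-point scale".
- **A further form.** The same section reports that "we added an econometric questionnaire of 8 items on the use of services for the purpose of the cost-effectiveness study". It gives no recall window for those items.
- **The schedule.** Table 3 (Measures) has two rows that could hold the treatment question: Help-seeking, listed as the GHSQ, and "Use of Health Services and Treatment questionnaire". Both are marked at pre-intervention, 6 months and 12 months. Neither is marked at 2 weeks.
- **The role.** The section Others outcomes lists use of treatment next to help-seeking behaviours among the other outcomes. The secondary hypothesis in Background expects the programmes to "increase emotional well-being and help-seeking behaviours, reduce bullying and cyberbullying at school".
- **The analysis.** The section Statistical analysis plans an unadjusted analysis of all outcomes after the intervention, relying on randomisation to balance baseline. Adjusted modelling with generalised estimating equations follows as needed.
- **The data.** The section Recruitment process links each pupil's answers over time by a code.

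**The concern.** A lifetime question describes history well at baseline but is a poor outcome when repeated. Once a pupil has truthfully answered yes, every later answer is yes. A pupil treated some years ago who seeks treatment again because of the programme looks the same as one who does nothing. Follow-up prevalence is therefore pre-trial treatment plus first-ever treatment since baseline, and only the second component can respond to the intervention.

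At stake is the reading of a null result. If the arms look alike on this item, a reader may conclude that the programmes did not move pupils towards treatment, when the question would have hidden much of such an effect. The other half of the instrument does not close this gap, because the GHSQ records what pupils intend to do and not what they have done.

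**Working it through.** **Inputs from the article.** Lifetime window (Help-seeking and use of treatment). Asked at baseline, 6 and 12 months (Table 3). 85 pupils per group (Sample size).

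**Inputs assumed.** The article gives no treatment rates. I take 12-month new treatment as c = 5% in controls and t = 15% in a programme arm, and L from 5% to 30%. I also assume that new treatment is unrelated to treatment history.

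**The plan's own figure.** The only design figure is 85 per group, for literacy scores, from a four-group one-way ANOVA with effect size 0.18. The noncentral F distribution gives power 0.799 at 85 per group, and 86 are needed to reach 80%, so the figure reproduces. It was not derived for this item. I use it only as an arm size.

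**Step 1: what the lifetime item shows.** At follow-up:

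- controls: L + (1 − L)c
- programme arm: L + (1 − L)t
- difference: (1 − L)(t − c)

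The difference always shrinks by the factor (1 − L), and the ratio moves towards 1.

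**Step 2: numbers.** At L = 20%, controls are 0.20 + 0.80 × 0.05 = 24.0% and the programme arm is 0.20 + 0.80 × 0.15 = 32.0%. The ratio is 32/24 = 1.33.

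Power is the two-sided 5% normal approximation for two proportions at 85 per arm, ignoring clustering: Φ[(d − 1.96·SE0)/SE1], where d is the difference, SE0 the pooled and SE1 the unpooled standard error.

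| Question asked | Control | Programme | Difference (points) | Ratio | Power |
|---|---|---|---|---|---|
| Bounded window | 5.0% | 15.0% | 10.0 | 3.00 | 0.59 |
| Lifetime, L = 5% | 9.8% | 19.3% | 9.5 | 1.97 | 0.42 |
| Lifetime, L = 10% | 14.5% | 23.5% | 9.0 | 1.62 | 0.32 |
| Lifetime, L = 20% | 24.0% | 32.0% | 8.0 | 1.33 | 0.21 |
| Lifetime, L = 30% | 33.5% | 40.5% | 7.0 | 1.21 | 0.15 |

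**Step 3: a smaller effect.** With 5% against 10%, the ratio of 2.0 becomes 1.49, 1.31, 1.17 and 1.10 at the same four values of L. At L = 20%, power goes from 0.23 to 0.09.

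**Step 4: the independence assumption.** If a share s of new treatment falls on pupils already treated, the visible difference is (1 − s)(t − c). Independence means s = L. If previously treated pupils are more likely to be treated again, s exceeds L and the dilution is worse. With s = 50%, the 10 points become 5.

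**Step 5: what linked data recover.** Among pupils who answered no at baseline, a later yes marks first-ever treatment. Under independence this restores 5% against 15%, but in fewer pupils. At L = 20%, 85 × 0.80 = 68 per arm remain, and the same formula gives (0.1000 − 1.96 × 0.0514)/0.0507 ≈ −0.02, a power of about 0.49. That compares with 0.21 for the unadjusted lifetime comparison and 0.59 for a bounded question.

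**The case against.** The strongest reply is that the hypothesis concerns help-seeking, that Table 3 gives the GHSQ as the help-seeking measure, and that the GHSQ is current and can move in either direction. This stands. The defect lies in one yes/no question, and a reader who infers that the trial cannot show any effect on help-seeking goes too far. What remains is that use of treatment is itself a listed outcome, and that the GHSQ measures intentions while the hypothesis speaks of behaviours.

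Three further replies stand in part:

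- **The linked data allow a repair.** The pupil code permits an analysis of no-to-yes changes, so the item is diluted but not uninformative. That analysis is not, however, the unadjusted comparison that the article describes, and it cannot recover repeat treatment.
- **The service-use items may have a recent window.** They may, but none is stated, and the article assigns them to the cost-effectiveness study. They can neither be counted on nor ruled out.
- **The rates are assumed and the trial was not sized for this item.** Both are true. With 5% against 10%, power is low even with a bounded window (0.23). The shrinkage by (1 − L) does not depend on c and t, although it does rest on independence.

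A reader might extend the point to bullying, because those items "ask whether a person has been a victim or a perpetrator of a bullying and/or a cyberbullying incident" and a fall is hypothesised. The article does not support this. The sentence paraphrases four study-specific items and says neither ever nor lifetime. The window is unstated, a detail an article commonly leaves to the questionnaire, so a cumulative item is not shown. Nor does the article assign the planned relative and absolute risk reductions to any particular outcome, so it cannot be said that those planned for this item are diluted.

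**Conclusion.** The point holds for the treatment-use question alone. Its stated lifetime window does not suit an outcome repeated at 6 and 12 months, and the unadjusted follow-up comparison is pulled towards no difference. If new treatment is independent of history, the risk difference shrinks by (1 − L). For an assumed 5% against 15%, a ratio of 3.0 falls to between 1.97 (L = 5%) and 1.21 (L = 30%). The direction and the shrinkage formula follow from the wording and that assumption, while every rate is illustrative. The power figures ignore school clustering, so true power would be lower throughout.

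Severity is minor. This is one item among the other outcomes, and no primary outcome or primary comparison is touched. It would be wrong to infer that the item is asked at every assessment, since Table 3 omits it at 2 weeks.

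**What to change.** - **Forms.** Keep the lifetime question at baseline and use the answer as a covariate. At 6 and 12 months, ask about treatment since the last questionnaire, and analyse that answer adjusted for baseline. Because the 2-week questionnaire does not carry this item, the 6-month form should make clear from which date the pupil is to count.
- **If the forms are already in use.** Analyse new yes answers among pupils who answered no at baseline, using the existing pupil code. Use the 8 service-use items as a measure of recent treatment only if they prove to have a bounded recall window.
- **Reporting.** Describe GHSQ results as help-seeking intentions, not behaviours.

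The cost is a few words on the follow-up forms and no added burden for pupils. The downside is that follow-up wording differs from baseline, so no change score can be formed. The fallback needs no new data, but it drops pupils treated before baseline and misses repeat treatment.

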### Stigma Behaviours and attitudes towards mental health

***Reported and Intended Behaviour Scale (RIBS)*** is used to assess reported and intended behavioural discrimination among the general public against people with mental health problems. The RIBS consist in 8 items; the first four items of the RIBS are designed to assess prevalence (past and current) of behaviour in each of the four contexts (1. living with; 2. working with; 3. living nearby; and 4.being in a relationship with someone with a mental health problem) while items 5–8 ask about intended (future) behaviour within the same contexts [34, 35]. For the purposes of this study, we selected four items from 5 to 8. It uses an ordinal Likert scale with five response options: “totally agree”, “somewhat agree”, “neither agree nor disagree”, “somewhat disagree”, “strongly disagree” from 5 to 1 points, respectively. The total score is obtained from a sum of the total answers ranging from 4 to 20. Higher scores indicate greater agreement with engaging the stated behaviour. The Spanish version will be used in this study.

***The Scaling Community Attitudes toward the Mentally Ill (CAMI)*** is an instrument for the systematic description of the attitudes of the community towards mentally ill people [36], which consists of 40 items divided into four dimensions (Authoritarianism; Benevolence; Community mental health ideology and Social restrictiveness). Only the “Authoritarianism” 10-item dimension in the Spanish version will be used [37]. Five of the 10 items are expressed as positive and five as negative. The score for each subscale is the sum of the positive items, and the reverse of the negative items. All items are scored on an ordinal scale (5–1), respectively, ranging from 10 to 50 for each factor. Higher scores mean greater agreement with engaging in the stated attitude.

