### Mental health symptoms and emotional well-being

***Strengths and Difficulties Scale (SDQ)*** (Spanish version) [38–40]. The SDQ consists of 24 items which generate scores along five subscales: emotional symptoms, conduct problems, hyperactivity-inattention, peer problems, and prosocial behaviour (positive mental health). Each item is rated 0, 1 or 2 points in accordance with being “absolutely true”, “somewhat true” or “not true”. The score is inverted in those items whose presence indicates positive features. The total score ranges from 0 to 50. It is suggested that individuals with scores above the cut-off (depending on each study population) should be evaluated more closely due to the increased risk of any alteration in mental health. The SDQ has been validated for use with adolescents aged 11–16 with a Cronbach’s alpha of 0.82 for the total difficulties scale [40, 41].

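### As worded, the GHSQ total counts the rating for 'no one' as help-seeking; the summed options and the handling of 'no one' need to be stated

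*Protocol article*

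**What the plan says.** The section Help-seeking and use of treatment says of the trial's instrument that "the second part includes the first item from the Spanish version of the" GHSQ. Intentions are rated from 1 to 7, with 7 the most likely, "for each help source option including “no one.” The sum of the points gives a total score ranging from 5 to 35". The next sentence gives the direction of the total: "Higher scores indicate higher help-seeking intentions". Nothing says that 'no one' is reversed or left out, and the help source options are not listed.

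Two other scales in the same article do have their oppositely keyed items dealt with. For CAMI, "The score for each subscale is the sum of the positive items, and the reverse of the negative items". For the SDQ, "The score is inverted in those items whose presence indicates positive features".

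The secondary hypothesis at the end of the Background expects that the programmes "will reduce mental health symptoms, increase emotional well-being and help-seeking behaviours". Table 3 schedules the GHSQ at baseline, 6 months and 12 months, among the outcomes that are not primary.

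**The concern.** A high rating on 'no one' means that the pupil would not seek help. A high rating on any real source means the reverse. If both go into one unreversed sum, the scoring rule conflicts with the stated direction of the score. The article gives a rule, a range and a direction, and read literally they do not fit together, so this is more than a detail left for the analysis plan.

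At stake is the only scored scale of help-seeking intentions in Table 3. A programme that works should raise the ratings of real sources and lower the rating of 'no one'. An unreversed sum sets the second change against the first and pulls the comparison towards no difference. If the rule is left open until the data are in, the choice of scoring could also be made with the results in view.

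**Working it through.** **Inputs from the article.** Each option is rated 1 to 7; the total runs from 5 to 35; higher means more help-seeking; 'no one' is among the rated options.

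**1. Reproduce the range.** A sum of k ratings of 1 to 7 runs from k to 7k. This gives 4 to 28 for k = 4, 5 to 35 for k = 5 and 6 to 42 for k = 6. The stated range therefore means exactly five summed ratings. If 'no one' is one of them, there are four real sources.

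**2. Score response patterns, taking 'no one' as one of the five.** As worded, the score is the sum of the four sources plus the 'no one' rating. Reversed, it is the sum of the four sources plus (8 minus the 'no one' rating). Excluded, it is the sum of the four sources only.

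| Pattern (four sources; 'no one') | As worded | Reversed | Excluded |
|---|---|---|---|
| 1,1,1,1; 7 (tells nobody) | 11 | 5 | 4 |
| 7,1,1,1; 1 (certain of one source) | 11 | 17 | 10 |
| 2,2,2,2; 1 (weak intentions) | 9 | 15 | 8 |
| 7,7,7,7; 1 (clearest help-seeker) | 29 | 35 | 28 |
| 7,7,7,7; 7 | 35 | 29 | 28 |

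A pupil who moves from the first row to the second changes by 0 as worded, by +12 if reversed and by +6 if excluded. As worded, the maximum of 35 needs the top rating for 'no one' as well.

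**3. Effect on a group comparison.** These are illustrative assumptions, not figures from the article: items have SD 1, sources correlate at r = 0.3 with each other and at -0.3 with 'no one', and the programme raises each source by 0.2 SD and lowers 'no one' by 0.2 SD.

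- Variance of the four-source sum: 4 + 12 × 0.3 = 7.6.
- As worded: (0.8 - 0.2) / √(7.6 + 1 - 2.4) = 0.6 / √6.2 = 0.24.
- Excluded: 0.8 / √7.6 = 0.29.
- Reversed: (0.8 + 0.2) / √(7.6 + 1 + 2.4) = 1.0 / √11 = 0.30.

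The loss is about 17% against exclusion and 20% against reversal.

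**4. Sensitivity to the assumed correlations.**

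| Between sources; with 'no one' | As worded | Excluded | Reversed | Loss |
|---|---|---|---|---|
| 0.2; -0.4 | 0.293 | 0.316 | 0.307 | about 5 to 7% |
| 0.4; -0.2 | 0.21 | 0.27 | 0.30 | about 22 to 29% |

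**5. When the effect vanishes.** The effect as worded is zero only if the mean fall on 'no one' equals the summed rise over the real sources. One case is a single source rising by as much as 'no one' falls, with the others unchanged. If the four sources rise equally, 'no one' would have to fall by four times the rise on each.

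**The case against.** The strongest reply is that the article never says which five ratings are summed. The range of 5 to 35 fits three rules: four sources with 'no one' unreversed, four sources with 'no one' reversed, or five real sources with 'no one' left out. The last two agree with the stated direction. The sentence that mentions 'no one' can also be read as describing how the parent questionnaire is answered, since it speaks of several problem types while the trial uses only the first item. Reversal stated for CAMI and the SDQ does not prove that none is intended here, and an article condenses its scoring rules.

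Much of this stands. A reader might infer that the trial will certainly add 'no one' unreversed; the text does not establish that. A reader might also infer that pupils who rely on nobody outscore good help-seekers in general, or that a real improvement is wiped out. Neither follows: such a pupil scores 11 against 29 for the clearest help-seeker, and exact cancellation is a special case.

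What does not stand is that the wording can be left alone. The sum follows directly on a rating that expressly includes 'no one', so a programmer following the text would add it. If another rule is meant, the text misdescribes it.

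**Conclusion.** The point holds as a fault in the scoring rule as worded. It is conditional on 'no one' being one of the five summed ratings, which the text suggests but does not settle. On that condition one fifth of the total is keyed the wrong way, and the usual consequence is dilution: about 5 to 30% of the standardised effect for correlations between 0.2 and 0.4 in size and equal item shifts. Those correlations and the 0.2 SD shift are assumptions.

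This should be fixed, but it is not critical to the trial. The Protocol article lists knowledge and stigma (EMHLT, RIBS, CAMI) as primary, and its sample size rests on MHL scores, so neither is affected. Help-seeking is one of several parts of the secondary hypothesis, and treatment and service use are collected at the same visits as the GHSQ.

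**What to change.** List the options that enter the GHSQ total and state how 'no one' is handled, by one of two rules:

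- Exclude 'no one' from the total and analyse it as a separate item on which lower is better. The range is 4 to 28 if it is one of the present five ratings, and stays 5 to 35 if there are five real sources.
- If 'no one' is one of the five, score it as 8 minus the rating and keep the range of 5 to 35.

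Apply the same rule at baseline, 6 months and 12 months, and fix it before outcome data by arm are seen. The cost is one sentence in the protocol or analysis plan and one line of scoring code. Each option is rated separately, so no new data are needed.

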### Statistical analysis

To analyse the effectiveness of the EspaiJove.net intervention, an experimental design will be created to evaluate the programme, randomised by clusters (schools) and with a control group on the waiting list. The statistical analyses to be performed will be as follows. A description of the sociodemographic variables of the sample at baseline will be done through a univariate analysis of the selected variables from the total sample and stratified by type of intervention. Then, to evaluate the effectiveness of all programmes and to achieve statistical significance for all outcomes after the intervention, an unadjusted bivariate primary analysis will be performed. Data scores after the intervention will be analysed with ANOVA, assuming that the baseline data will be similar due to the randomisation process across groups. Finally, a multivariate and adjusted analysis, as necessary, will be employed to evaluate the effectiveness of those programmes so as to achieve statistical significance after the intervention. Data will be analysed with Generalised Equation Estimates (GEE) to assess the efficacy of the intervention. This statistical model is appropriate for longitudinal clustering analyses since this study design (schools) will allow us to consider the individual data correlation within the same cluster group. Analyses will be based on an intention-to-treat analysis.

We will also examine relative and absolute risk reduction, (RRR) and (ARR), respectively. Additionally, to analyse the acceptability and satisfaction of each programme, a descriptive analysis will be performed to observe the percentage of acceptability and satisfaction. Statistical analyses will be performed using the SPSS [48].

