**Methods:**

A school-based clustered randomised controlled trial (cRCT) design with 12 months of follow-up. **Subjects:** At least 408 secondary school students who attend the 3rd year of E.S.O (Compulsory secondary education for 13- to 14-year- olds) will be recruited from 8 schools within Barcelona city, Catalonia (Spain). **Intervention:** A dose-response intervention will be delivered with 4 arms: 1) Sensitivity Programme (SP) in Mental Health (1 h); 2) Mental Health Literacy (MHL) Programme (6 h); 3) MHL plus first-person Stigma Reduction (MHL + SR) (7 h); 4) Control group: waiting list.

**Primary outcomes:** 1) MHL: EspaiJove.net MHL Test (EMHLT); 2) Stigma: Reported and Intended Behaviour Scale (RIBS) and Community Attitudes toward the Mentally Ill (CAMI). **Others outcomes:** 1) Acceptability of intervention; 2) Mental health symptoms and emotional well-being (SDQ); 3) States of Change Scale (SCS); 4) Bullying and Cyberbullying; 5) Quality of life (EQ-5D); 6) Help seeking and use of treatment; 7) Health benefits.

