### Recruitment process

The recruitment process for the trial began in September 2016. All eligible secondary schools within Barcelona city are contacted and encouraged to participate in the study. Emails providing information about the study are sent to all schools, and among those schools that had shown an interest in participating, a presentation is delivered at the school by two project researchers. Once a school agreed to participate, consent letters are sent out to the parents of all participating students.

Out of all the schools that accept participation in the study, a cluster randomisation by school and individual students as participants is conducted. The total sample estimated within a minimum of 408 adolescents will be divided into three experimental groups and one control waiting list. The randomisation assignment will be carried out through a computer program, and the group assignment will be 1:1:1:1.Each interviewer blinded the assessments.

Pre-treatment questionnaires will be completed approximately 2 weeks before the intervention by all students (intervention and control groups). A code will be used to match participant answers over time whilst preserving anonymity. One teacher will be the unique person responsible for keeping the identification number and corresponding student. Two researchers will be responsible for supplying each student with a questionnaire for its completion during each assessment within the study. The class teacher will be present in the classroom during the questionnaire administration involved in the data collection with the aim of minimising missing data and errors when providing the questionnaires.

A second evaluation will be performed approximately 2 weeks after the intervention. A third and fourth evaluation will be examined at 6 and 12 months, respectively. Table 2 shows the data collection and intervention programme timelines.

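### The analysis labelled primary is an unadjusted pupil-level ANOVA with no term for school, although schools are randomised; unless the ICC is close to zero, its true type I error is well above 5%

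*Protocol article*

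**What the plan says.** The Statistical analysis section of the protocol article describes the trial as "randomised by clusters (schools) and with a control group on the waiting list". It then says that "an unadjusted bivariate primary analysis will be performed. Data scores after the intervention will be analysed with ANOVA", and justifies comparing follow-up scores alone by expecting randomisation to balance baseline. No term for school appears in this step.

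A last step follows, quoted here without the end of its sentence: "a multivariate and adjusted analysis, as necessary, will be employed to evaluate the effectiveness of those programmes so as to achieve statistical significance after". The next sentences name GEE as the method for assessing efficacy and give correlation within schools as the reason for choosing it.

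On the layout, the abstract says pupils "will be recruited from 8 schools within Barcelona city" and that "A dose-response intervention will be delivered with 4 arms"; Recruitment process adds that "the group assignment will be 1:1:1:1". The Sample size section uses a one-way ANOVA with effect size 0.18, alpha 0.05 and 80% power, giving 85 pupils per group (340), raised to 408 for 20% attrition. It mentions neither an ICC nor a design effect.

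**The concern.** Pupils in one school share teachers, intake and neighbourhood, so their scores tend to be correlated. When whole schools are allocated, that shared component falls entirely within one arm and adds to the variance of the arm means. A pupil-level ANOVA judges arm differences against pupil-to-pupil variation only and takes the extra variance for a treatment effect. Randomisation makes the arms comparable in expectation; it does not make pupils within a school independent.

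With few schools per arm, little of the school variation averages out. The main conclusion on literacy and stigma is at stake, and the Discussion says that a positive result would lead to use in further Barcelona schools. Two analyses also address the same question, and the text does not say which one prevails if they disagree.

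**Working it through.** **Inputs.** From the protocol: 8 schools, 4 arms, 1:1:1:1 allocation, 408 pupils recruited, 340 required before the attrition allowance, effect size 0.18, alpha 0.05. Derived: 8/4 = 2 schools per arm; 408/8 = 51 and 340/8 = 42.5 pupils per school. Assumed: the ICC, equal school sizes and normally distributed school effects.

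**1. The plan's own figure.** For a one-way ANOVA with independent pupils, the noncentrality is λ = f²N = 0.18² × 340 = 11.02. On 3 and 336 degrees of freedom the power is 0.799, and 86 per group is the first whole number to reach 0.80. So 85 per group reproduces within rounding, with f = 0.18 and no design effect. The 408 is 340 × 1.2. The trial is therefore sized for the same clustering-free test that the analysis section calls primary.

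**2. True type I error of that test.** Let m be pupils per school, total variance 1, and DE = 1 + (m − 1) × ICC. Under the null:

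- between-arm mean square ~ DE × χ²(3)/3
- within-arm sum of squares ~ DE × χ²(4) + (1 − ICC) × χ²(8(m − 1))
- the ANOVA rejects when the ratio of mean squares exceeds the 5% point of F(3, 8m − 4), which is 2.63

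The middle line shows the fault: only 4 degrees of freedom carry school variation, but the test uses 404 (m = 51) or 332 (m = 42).

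| ICC (assumed) | DE, m = 51 | True error, m = 51 | DE, m = 42 | True error, m = 42 |
|---|---|---|---|---|
| 0 | 1.00 | 5% | 1.00 | 5% |
| 0.005 | 1.25 | 10% | 1.21 | 9% |
| 0.01 | 1.50 | 16% | 1.41 | 14% |
| 0.02 | 2.00 | 27% | 1.82 | 23% |
| 0.05 | 3.50 | 53% | 3.05 | 47% |

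Simulation with 200,000 null trials per cell agrees to within about half a percentage point.

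**3. A valid test in this layout.** An F test on the eight school means has 8 − 4 = 4 error degrees of freedom and holds 5% under these assumptions, with critical value 6.59. Its power uses λ = 11.02/DE, with DE = 1 + 41.5 × ICC:

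| ICC | DE | λ | Power, F(3, 4) |
|---|---|---|---|
| 0.01 | 1.415 | 7.79 | 0.292 |
| 0.02 | 1.830 | 6.02 | 0.235 |
| 0.05 | 3.075 | 3.58 | 0.157 |

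**4. Would the GEE do instead?** With two equal schools per arm, the uncorrected sandwich estimate of an arm mean's variance is on average half the true value. The Wald statistic for one pairwise contrast is then √2 × t(2), so the null rejection rate is P(|t(2)| > 1.96/√2) = 30%, whatever the ICC. For the joint 3-df test, 100,000 simulated null trials gave 63%.

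**The case against.** The strongest defence is that clustering is not overlooked. The same section plans a GEE, says it assesses efficacy, and defends it by within-school correlation. *Primary* could mean no more than the first step in a sequence. The sentence that names GEE carries no condition, and the qualifier on necessity may refer only to covariates. The phrase about reaching significance also appears in the preceding step, applied to all outcomes before anything could have been selected, so it may be loose English for testing significance.

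Much of this stands. A reader might infer that the cluster-aware model will be run only for programmes that pass the ANOVA. The wording permits that, but the documents do not establish it. A reader might also infer that the plan ignores clustering altogether; the GEE shows otherwise.

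The defence does not remove the defect. On the kindest reading, the analysis that carries the label *primary* is still the one without school, the Sample size section relies on the same test, and nothing gives the GEE precedence. This is a method that the article states, not a detail left to a fuller document.

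Two cautions on size also stand. A several-fold inflation is not a fact independent of the ICC: it is about two-fold at 0.005 and absent at zero. And two schools per arm is derived, not stated. The Sample section speaks of classes and several randomisations by stratum, which blurs the unit, whereas Study design, Recruitment process and Statistical analysis point to schools. If classes were allocated, the percentages would change, but pupils would still be clustered.

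**Conclusion.** The point holds, and it should be corrected before the data are analysed. In a school-randomised trial, the test labelled primary treats pupils as independent. On the assumed layout, the inflation of the 5% level is about two-fold at ICC 0.005, three-fold at 0.01, five-fold at 0.02 and roughly nine- to eleven-fold at 0.05. Only an ICC of practically zero would make it harmless, and the plan's own reason for using GEE is that scores within a school are correlated. School differences may therefore be declared programme effects; the documents do not show that they will be. Whether the GEE is optional or result-dependent is an ambiguity to close, not an established fault.

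**What to change.** - Remove the pupil-level ANOVA as the primary test. Keep it at most as a descriptive table without p-values.
- Name one primary analysis that respects school clustering and uses small-sample inference: for example a baseline-adjusted analysis of school summaries, or a mixed model with a random school effect, tested on about 4 error degrees of freedom. Adjust for baseline at pupil level where possible, since a school-level covariate would use one of the four.
- Do not use an uncorrected sandwich GEE for this role.
- Run the primary analysis unconditionally for all three programmes. Strike the qualifier on necessity and the phrase about reaching significance.
- State that allocation is by school, and reconcile the Sample section with this.

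The rewording is cheap; the consequence is not. Confidence intervals will be much wider. With 340 pupils in eight schools, power at f = 0.18 is roughly 29% at ICC 0.01 and 16% at 0.05, so the stated 80% must be restated with an explicit ICC. The choice is between recruiting more schools and openly accepting the lower power.
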